**6.3. Sample Calculation**

To determine the sample size of the study, data from a pilot study that followed the methodology proposed in this research project was used, with four participants, three (75% of the sample) being female and one (25% of the sample) of the sample. male, with mean age of 31 years and standard deviation of ± 1.91. In the pilot study, 16 teeth were randomly assigned to one of the four groups with the Research Randomizer Calculator (www.socialpsychology.org/randomizer.htm).

The VAS was used to measure sensitivity, considering a clinically relevant difference of three units between the initial and final VAS scores, according to a previous study (20). The G Power® program (Heinrich-Heine-Universität Düsseldorf, Germany) was used for mixed ANOVA, considering a statistical power of 80%, α error of 5% and prediction of sample loss at the end of the study of 20%. The resulting sample for this study was 80 teeth, 20 teeth per group.

[figure not shown]

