**Flowchart 01. Recruitment and allocation scheme performed in the pilot study**

**6.4. Study design**

After randomization of the sample, the teeth (at least 20 for each group) will be allocated to one of the four assessment groups according to the scheme below:
[figure not shown]

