## **6.8. Assessment of pain sensitivity**

For the evaluation of pain sensitivity, the visual analogue scale (EVA) of 10 cm in length will be used, where 0-pain is absent and 10-pain is extreme. Requesting the participant to signal the number compatible with the pain sensation after application of the stimuli, evaporative (triple syringe) and tactile (exploratory probe). Sensitivity assessment will be done in five moments: Immediately before starting treatment, after the first session, after the second session, after the third session and after one month of treatment.

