## **6.9. Statistical analysis**

### The values ​​corresponding to the sensitivity reported by the participants were tabulated in an Excel spreadsheet (Microsoft Windows, 2010) and analyzed with the IBM SPSS Statistics for Windows 22.0 program (IBM Corp., New York, United States). Considering the parametric data of this study, if it has normal distribution of the same to the intergroup analysis will be done with mixed ANOVA, and the specific intergroup comparison will be done with the Tukey post-hoc test. If the data are abnormal distribution the intragroup comparison will be performed from the Friedman test and the intergroup by the Wilcoxon test. A significance level of 5% will be set for all analyzes to be performed.

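### Section 6.9 ties the Tukey comparison to no visit and leaves baseline VAS unadjusted; run as a main-effect post-hoc test, it would average in the pre-treatment score

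*Protocol*

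**What the plan says.** Section 6.8 of the protocol lists five VAS assessments: "Immediately before starting treatment, after the first session, after the second session, after the third session and after one month of treatment". So one of the five repeated measurements precedes any treatment.

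Section 6.9 says that, if the data are normally distributed, "the intergroup analysis will be done with mixed ANOVA", and that "the specific intergroup comparison will be done with the Tukey post-hoc test". The data are to be "analyzed with the IBM SPSS Statistics for Windows 22.0 program". The section names no baseline covariate, change score or visit for the pairwise step.

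Two other places show what the trial wants to learn. Section 6.3 sizes it on a three-unit VAS difference between the first and last assessments. Section 5 states the null hypothesis over one month of evaluation.

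**The concern.** A Tukey test on the between-group factor of a mixed ANOVA usually compares arm means averaged over all the repeated measurements. Here that average would include a score taken before treatment, when the arms can differ only by chance. The pairwise result would then describe an average level over five occasions. The sample size was built on a change to the last visit.

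The wording also allows Tukey at each visit, which does not have this problem. On either reading, though, the baseline score is collected and then not used to sharpen the comparison between arms. At stake are the meaning of the pairwise results and their precision, in a trial of 20 teeth per group.

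**Working it through.** **The plan's own figure.** Section 6.3 gives 80 teeth, 20 per group, for 80% power, 5% alpha and 20% loss. This cannot be reproduced, because the effect size f, the SD and the within-tooth correlation are not stated. Working back from 80 × 0.8 = 64 evaluable teeth at correlation 0.3 / 0.5 / 0.7, f would be 0.283 / 0.330 / 0.372 for the between-group term, or 0.199 / 0.168 / 0.130 for the group-by-time term. The document does not say which was meant.

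**Inputs.** Five assessments, one of them pre-treatment (6.8); four arms (6.4), hence 4 × 3 / 2 = 6 pairs. Assumed: compound symmetry with common SD σ and correlation ρ between visits, and independent units.

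**Share of the effect kept by the five-visit mean**, as a fraction of the one-month effect:
- constant from session 1: (0 + 1 + 1 + 1 + 1) / 5 = 0.80
- even build-up: (0 + 0.25 + 0.50 + 0.75 + 1) / 5 = 0.50
- present at one month only: 1 / 5 = 0.20

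Including baseline explains only part of the last two. With an even build-up, the mean of the four post-treatment visits is already 2.5 / 4 = 0.625, and adding baseline lowers it to 0.50.

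**Variances, in units of σ²:**
- five-visit mean: (1 + 4ρ) / 5
- mean of four post-treatment visits, baseline as covariate: (1 + 3ρ) / 4 − ρ²
- one month, baseline as covariate: 1 − ρ²
- one month, unadjusted: 1

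| ρ | five-visit mean | adjusted post-treatment mean | adjusted one month |
|---|---|---|---|
| 0.3 | 0.440 | 0.385 | 0.910 |
| 0.5 | 0.600 | 0.375 | 0.750 |
| 0.7 | 0.760 | 0.285 | 0.510 |

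**Relative sample size.** The required number is proportional to variance / effect².
- *Five-visit mean against adjusted post-treatment mean.* The baseline effect is zero, so the five-visit effect is always 4/5 of the post-treatment effect, whatever the profile. The ratios are (0.440 / 0.64) / 0.385 = 1.79, (0.600 / 0.64) / 0.375 = 2.50 and (0.760 / 0.64) / 0.285 = 4.17.
- *Five-visit mean against adjusted one-month contrast, constant effect.* 0.6875 / 0.910 = 0.76, 0.9375 / 0.750 = 1.25 and 1.1875 / 0.510 = 2.33. Break-even is at 1 + 4ρ = 3.2(1 − ρ²), so ρ is about 0.41.
- *The same, even build-up.* (0.440 / 0.25) / 0.910 = 1.93, (0.600 / 0.25) / 0.750 = 3.20 and (0.760 / 0.25) / 0.510 = 5.96.
- *If Tukey is run at each visit:* unadjusted against adjusted one month, 1 / (1 − ρ²) = 1.10, 1.33 and 1.96.

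**Power illustration.** Assumed: SD 3, ρ = 0.5, a three-unit difference between two arms at one month, 20 × 0.8 = 16 independent teeth per arm, and two-sided 5% per comparison. Tukey adjustment would lower every figure.

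| Effect profile | five-visit mean | adjusted post-treatment mean | adjusted one month | unadjusted one month |
|---|---|---|---|---|
| constant | 83% | 99.6% | 90% | 81% |
| even build-up | 45% | 82% | 90% | 81% |
| one month only | 11% | 21% | 90% | 81% |

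**The case against.** The strongest reply is that section 6.9 never says that Tukey is applied to means over five visits. A reader might infer it from usual software behaviour, but visit-by-visit Tukey fits the text equally well and dilutes nothing. This stands, so the dilution is conditional on one reading.

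A reader might also infer that baseline information is thrown away altogether, or that the comparison is biased toward zero. The document does not support either. The group-by-time interaction in the mixed ANOVA uses the baseline score, so the loss concerns the pairwise step. Chance baseline imbalance under randomisation is imprecision, not bias. A five-visit mean is a different quantity from the one-month effect and need not be smaller: with effects of 0, 1, 1, 1 and 0.5 it is 3.5 / 5 = 0.70, above the one-month value of 0.50.

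It would be wrong to credit the 1.8 to 4.2 ratios to a one-month contrast. They belong to the adjusted post-treatment mean. With a constant effect and low correlation, the one-month contrast needs more units than the five-visit mean.

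Two additions are tempting. One is that units with a missing visit would be dropped while 20% loss is expected. The other is that the two stimuli would be tested separately, given that "A significance level of 5% will be set for all analyzes to be performed". Section 6.9 states neither procedure, so neither belongs to this point. Nor does the document give a reason to prefer one stimulus as primary.

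Finally, covariates and contrasts are often left to a statistical analysis plan. Missing detail alone would not be a finding. What remains is that the method 6.9 does fix, on one natural reading, does not answer the question set in 5 and 6.3, and on either reading leaves baseline unadjusted.

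**Conclusion.** The point holds in a conditional form and is worth correcting. As written, the Tukey comparison has no visit and no baseline adjustment. Run as a main-effect post-hoc test, it keeps 80% of a constant effect. It then needs about 1.8 / 2.5 / 4.2 times the units of the baseline-adjusted post-treatment mean at correlation 0.3 / 0.5 / 0.7, and it misses the change on which the trial was sized. Run at each visit, it loses only the gain from adjustment, a factor of 1.10 / 1.33 / 1.96 at one month.

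The 80% is plain arithmetic. The ratios rest on compound symmetry and on correlations that the protocol does not give. The entry threshold of VAS 4 or more (Table 01) narrows the baseline range and may lower the baseline correlation, and with it the gain. The calculations treat teeth as independent; clustering of teeth within participants is a separate matter.

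**What to change.** Reword section 6.9 as follows:
- Use the four post-treatment VAS assessments as outcomes and baseline VAS as a covariate, by ANCOVA or by a mixed model with arm, visit and arm-by-visit.
- Name in advance the baseline-adjusted contrast on which the arms are compared. One month matches sections 5 and 6.3; the adjusted mean of the post-treatment visits can be supportive.
- Apply multiplicity control, Tukey or an equivalent, over the six arm pairs on that contrast.

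The cost is wording only: no new data or visits are needed. The one real downside is that a single-visit contrast may lose some power against an average if the effect is constant and the between-visit correlation is low (below about 0.41 under the assumptions above).

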**RESEARCH PROJECT**

**5 – AIM**

The aim of this study was to evaluate the effect of the fluorinated amorphous calcium phosphate casein-phosphorus (CPP-ACPF) associated with low-power laser therapy (TLBP) on the symptomatology and impact of the quality of life of patients with dentin hypersensitivity ( HD) by means of a randomized, parallel, placebo-controlled clinical trial. The null hypothesis tested in the present study will be:

H0 - there will be no difference in the manifestation of dentin hypersensitivity between the groups treated with TLBP, CPP-ACPF or placebo, associated or not, during one month of evaluation, and will not influence the participants' quality of life.

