**6.5. Randomization**

The participants, with at least two teeth with HD equal or superior to four in the EVA, will be allocated through a block randomization aiming to balance the sample number in the amount of existing arms. For each block a total of four participants were defined, and after the formation of the block, a numerical draw among the participants was carried out and, subsequently, each 01 volunteer was allocated to compose one of the four groups under different arrangements (A4,1 , A3.1, A2.1 and 1) (Figure 01). The total number of blocks will be ± 10.

Allocation secrecy will be maintained throughout the sampling composition process. One of the project's collaborators will be responsible for the formation of the block, numerical draw within the block and allocation in the groups. The numerical draw will be done using numbered and coded papers, of which the participants, the principal investigator, the clinical operator and the evaluator will not be aware of the group to which the participant will be allocated.

[figure not shown]

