### To analyze non-parametric QEHD data the Wilcoxon test will be used.

**7 - GOALS**

### The present project aims to be developed within the timeframe set forth in the schedule and to start after approval by the bioethics committee. The bibliographic review will be done from September 2017 until December 2018, the work will be submitted to the bioethics committee and inserted in an international clinical records site between August and September 2017, followed by the screening period from October until November 2017. Upon completion of the screening, the randomized clinical trial will be conducted from November 2017 through September 2018. After data collection is completed, statistical analysis of the results will be done from October 2018 through November 2018. The final report will be built and submitted by December 2018 and later the scientific paper will be written for publication.

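### The non-normal fallback in section 6.9 gives the four-arm VAS comparison to an unspecified Wilcoxon test, and neither form of that test provides a 5% test of the four-group null hypothesis

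*Protocol*

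**What the plan says.** Section 5 describes the study as conducted "by means of a randomized, parallel, placebo-controlled clinical trial". Its null hypothesis is that "there will be no difference in the manifestation of dentin hypersensitivity between the groups treated with TLBP, CPP-ACPF or placebo", with combined treatment included. Table 2 lists four arms. Section 6.5 allocates participants in blocks of four, where "each 01 volunteer was allocated to compose one of the four groups under different arrangements".

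Section 6.9 has two branches for the VAS. If the data are normal, "the intergroup analysis will be done with mixed ANOVA, and the specific intergroup comparison will be done with the Tukey post-hoc test". The second branch reads: "If the data are abnormal distribution the intragroup comparison will be performed from the Friedman test and the intergroup by the Wilcoxon test". No omnibus test for four groups and no adjustment for pairwise comparisons is named in the second branch. For both branches, "A significance level of 5% will be set for all analyzes to be performed".

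The last sentence of section 6.9 uses the same test name again: "To analyze non-parametric QEHD data the Wilcoxon test will be used". Section 6.8.3 collects that questionnaire before treatment and at one month.

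**The concern.** The null hypothesis concerns four independent groups, while every test called Wilcoxon compares two samples. The name covers two procedures: signed-rank for paired data and rank-sum for independent data. The protocol does not choose between them, and each fails here for a different reason. Signed-rank has no pairs to work on. Rank-sum has to be repeated over pairs of arms, with nothing to hold the overall error at 5%.

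If the VAS data go to this branch, it carries the whole between-arm conclusion on pain. Control of the error rate would then depend on the outcome of a normality check: present under mixed ANOVA with Tukey, absent otherwise.

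**Working it through.** **Inputs from the protocol**
- Four arms, one participant per arm in each block of four, about 10 blocks (6.5).
- 80 teeth, 20 per arm, allowing for 20% loss (6.3); at least 20 teeth per arm (6.4).
- Two to four hypersensitive teeth per participant (Table 01).
- Two stimuli and five assessments, four of them after baseline (6.8).
- 5% for each analysis (6.9).

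**The plan's own figure.** 64 / (1 - 0.20) = 80, so 80 teeth is consistent with 64 evaluable teeth, 16 per arm. The calculation cannot be taken further back because the SD, the effect size f and the repeated-measures correlation are not given. It is used here only to set 16 teeth per arm in the simulations.

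**Rank-sum reading**
- Number of pairs: 4 × 3 / 2 = 6.
- If the six tests were independent: 1 - 0.95^6 = 0.265. They share arms, so the true figure is lower.
- Simulation under the null (3,000 trials, four arms of 16 independent teeth, assumed skewed and bounded VAS-like scores): at least one of six rank-sum tests was significant in 19.3% of trials. The Monte Carlo standard error is √(0.193 × 0.807 / 3,000) = 0.7 percentage points.
- A separate simulation with 20 per arm, using t-tests as a stand-in for rank-sum, gave 20%.
- Kruskal-Wallis on the same data as the first simulation rejected in 4.7% of trials.

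**Signed-rank reading**, with teeth in different arms paired arbitrarily
- Error of one comparison under the null: 4.6%, against 4.8% for rank-sum.
- All six pairs: 19.4%, so the multiplicity problem is the same.
- With one arm shifted by an assumed 2 VAS units (2,000 trials): power 63.8%, against 67.6% for rank-sum.
- Pairing the same data a second time at random changed significance in 3.4% of trials under the null and in 14% under the 2-unit shift.
- The test also needs equal numbers in the two arms. With a minimum of 20 teeth per arm, two to four teeth per participant and 20% expected loss, equality cannot be assumed. Unmatched teeth would have to be discarded.

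**Why a tooth-level omnibus test is not enough.** With two teeth per participant and an assumed intraclass correlation of 0.5 (null, 2,000 trials), the error of one comparison rose to about 10% for both Wilcoxon tests. The six-pair error rose to about 37%, and tooth-level Kruskal-Wallis rejected in 16.7%. A replacement therefore has to work at participant level or model the clustering.

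**What the move to participants costs.** About 10 blocks give about 10 participants per arm, or 10 × 0.8 = 8 after the expected loss. Under the same assumptions the design effect is 1 + (2 - 1) × 0.5 = 1.5, so 20 teeth carry the information of 20 / 1.5 = 13.3 independent teeth. Ten participant means, each with variance (1 + 0.5) / 2 = 0.75 of a single tooth's, carry the same: 10 / 0.75 = 13.3. Averaging loses little information that the tooth count really held.

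**The case against.** **The test may be the right two-sample test.** Section 6.9 assigns it to the comparison between groups, which favours rank-sum. The pre/post use for the questionnaire, and the place beside Friedman, favour signed-rank. A reader might infer that the protocol has plainly chosen a paired test, but the text leaves the variant open. This stands, and it is why both readings are worked through.

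**One pairwise comparison is not invalid.** A reader might conclude that the fallback cannot validly test anything. That is too strong: even on arbitrary pairs, signed-rank kept about 5% error for one comparison of independent teeth. The fault lies in the arbitrary result and in the four-group hypothesis, not in every single p-value.

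**The fallback may never be used.** Non-normality is only a condition in section 6.9. The sample size in 6.3 is based on mixed ANOVA, and no VAS mean, SD or distribution is given. The scale is bounded and teeth enter at 4 or more, so a floor effect is conceivable. The protocol gives no figures to call it likely.

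**Pairs could come from the blocks.** Each block holds one participant per arm, so matching participants within a block is possible in principle. The plan does not say to do this, and blocks match participants, not teeth. Section 6.4 speaks of allocating teeth, whereas 6.5 allocates participants. Independence of the arms rests on 6.5 and on the parallel design in section 5, and the two sections should be reconciled.

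**Multiplicity may be left to an analysis plan.** Detail often is. Here, however, the protocol itself names the test and sets 5% for every analysis, and it does provide Tukey in the other branch.

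**Friedman is not offered as a between-group test.** The protocol labels it intragroup, so its presence is not an error.

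**Conclusion.** The point holds for the non-normal branch as written. Read as signed-rank, the test needs pairs that the design does not define between arms. Read as rank-sum, it covers two of four arms, with no omnibus test and no stated adjustment. Either way, six pairwise tests at 5% give about 19-20% familywise error at one visit for one stimulus, assuming independent teeth and 16 to 20 per arm. The upper figure, if the tests were independent, is 26.5%. Within-participant correlation would raise the error further; the 37% figure depends on the assumed correlation of 0.5 and two teeth each.

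A reader might multiply up to 6 × 4 × 2 = 48 tests over all post-baseline visits and both stimuli, for which a simulation gave 67-75%. The documents do not support quoting that as the trial's error rate. Section 6.9 does not prescribe that family of tests, and the figure rests on assumed correlations.

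**What to change.** In section 6.9, replace the between-group Wilcoxon wording of the non-normal branch with one of the following, chosen before the data are seen:

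1. Kruskal-Wallis across the four arms on one value per participant, for example the mean change in VAS over that participant's study teeth at one month. Follow it with pairwise Dunn or Mann-Whitney comparisons (name one) with Holm correction over the six pairs.
2. A rank-based or permutation analysis that keeps each participant's teeth together and permutes arm labels within the blocks of four.

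State that the Friedman results describe change within arms and are not evidence on the between-group null hypothesis. For the questionnaire, say which Wilcoxon test is meant. Reconcile sections 6.4 and 6.5 on whether teeth or participants are allocated.

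The cost is wording only, with no new data. Adjusted p-values will be larger, and the analysis unit in this branch becomes the participant, about 10 per arm, instead of the tooth.

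### Air VAS, tactile VAS and QEHD are each tested at a full 5% against one null hypothesis with none primary, and the rank-based fallback leaves the arm pairs unadjusted, so the decision on that hypothesis is not held at 5%

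*Protocol*

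**What the plan says.** **Hypothesis (section 5).** The sensitivity part states that "there will be no difference in the manifestation of dentin hypersensitivity between the groups treated with TLBP, CPP-ACPF or placebo", alone or combined, over one month. The same sentence goes on to include quality of life.

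**Outcomes (6.8, 6.8.3).** VAS is recorded after an evaporative and a tactile stimulus. "Sensitivity assessment will be done in five moments": before treatment, after each of three sessions, and at one month. The QEHD is completed before treatment and at one month. None of these is ranked.

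**Analysis (6.9).** Normal data go to a mixed ANOVA with Tukey for the specific arm comparisons. Non-normal data go to Friedman within groups and Wilcoxon between groups. The QEHD has its own Wilcoxon test. The level is fixed in one sentence: "A significance level of 5% will be set for all analyzes to be performed".

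**Sizing (6.3).** The calculation uses a mixed ANOVA with 5% alpha and 80% power, "considering a clinically relevant difference of three units between the initial and final VAS scores", and ends with: "The resulting sample for this study was 80 teeth, 20 teeth per group". It does not say which stimulus the VAS difference refers to.

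**The concern.** A between-arm difference on air VAS, on tactile VAS or on the QEHD would each contradict the single hypothesis in section 5, and each is tested at the full 5%. The error rate of the decision is therefore the chance that any one of the three rejects, which exceeds the 5% used for sizing. The fallback adds a second layer, because Tukey's protection of the arm pairs disappears and nothing replaces it.

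At stake is a false claim that a treatment works. A mixed result, with one stimulus positive and the other not, would also have no planned interpretation.

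**Working it through.** **Inputs from the protocol.** Level 5% per analysis (6.9); four arms (6.4); two stimuli (6.8); QEHD (6.8.3, 6.9); 20 teeth per arm (6.3). The protocol gives no correlation between outcomes and no VAS standard deviation, so the correlations below are assumptions.

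**1. The plan's own figure.** For one test, such as the group-by-time test of a mixed ANOVA on one stimulus, the stated 5% holds. Simulated under no effect (4,000 runs, 20 independent units per arm, correlation 0.5 between visits), the rejection rate is 4.6% to 5.1%.

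**2. Parametric route, across outcomes.** With k independent tests at 5%, the chance of at least one false rejection is 1 − 0.95^k.

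- Two stimuli: 1 − 0.95² = 9.75%.
- Two stimuli and QEHD: 1 − 0.95³ = 14.3%.
- Ceiling for three tests under any correlation: 3 × 0.05 = 15%.

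Correlation lowers this. Two simulations under no effect, each with one between-arm test per outcome:

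| Simulation | Assumed correlation between outcomes | At least one rejection |
|---|---|---|
| Four-arm F test per outcome, 10 units per arm, 20,000 runs | 0 / 0.5 / 0.8 | 13.8% / 12.7% / 10.2% |
| Group-by-time test per stimulus plus four-arm F test on QEHD, 20 units per arm, 4,000 runs | 0 / 0.3 / 0.5 / 0.7 | 15.2% / 14.2% / 13.3% / 13.1% |

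The 15.2% is simulation noise around 14.3%: the standard error is √(0.143 × 0.857 / 4,000) = 0.55 percentage points. Both simulations use an F test for the QEHD where the protocol names Wilcoxon, so they give the approximate size only.

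**3. Fallback route, across arm pairs.** Four arms give 4 × 3 / 2 = 6 pairs. If the six tests were independent, the chance would be 1 − 0.95⁶ = 26.5%. Pairs that share an arm are correlated, so the true figure is lower. Simulated with two-sample rank tests, 20 independent units per arm, one visit and one stimulus, it is 19% to 21%. Friedman compares visits within an arm, so it does not act as an overall between-arm test that must reject first.

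**4. The remedy.** Splitting alpha gives 0.05 / 3 = 0.0167 per outcome. Then 1 − (1 − 0.0167)³ = 4.9% if independent, and at most 5% under any correlation. A fixed sequence headed by one primary test also holds 5%.

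**5. Sample size.** 16 / (1 − 0.20) = 20 per arm, so the stated total is consistent with 16 evaluable teeth per arm. The 16 cannot be derived, because the only standard deviation in 6.3 is for age. These figures neither confirm nor refute the sample size.

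**The case against.** **Most of the multiplicity is already handled.** On the parametric route this is right: the mixed ANOVA takes the five assessments into one model and Tukey covers the six pairs. A reader might infer that each visit is a further chance to reject, which for two stimuli at four post-baseline visits plus QEHD would give 1 − 0.95⁹ = 37% (18% at correlation 0.8). The documents do not support that count, since no section plans a separate four-arm F test at each visit. On the fallback route the protocol does not say at which visits Wilcoxon is applied, so the figure here is kept to one visit and one stimulus.

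**The sizing points to an outcome.** Partly right. A reader might infer that the 80% power is tied to no endpoint. Section 6.3 does tie it to initial versus final VAS; only the stimulus is left open.

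**Ranking of outcomes may sit in an unseen SAP, and 5% per test is a conventional statement.** An SAP could rank the outcomes, and for that reason it cannot be shown that the headline result will be chosen after the data are seen. But the protocol itself sets both the hypothesis and the level for all analyses. An SAP that split alpha would have to depart from 6.9 as written.

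**Section 5 may hold two hypotheses, not one.** The translated sentence allows this. Sensitivity alone still has two unranked stimuli: 9.75% if independent, and 8.6% to 10.6% in simulation over correlations 0 to 0.7.

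**Conclusion.** The point holds in limited form. Followed as written on the parametric route, the plan rejects a true joint hypothesis in about 10% to 15% of trials, two to three times the stated 5%. On the rank-based route, six unadjusted pairwise tests give about 20% for a single visit and stimulus, before the second stimulus or the QEHD is counted.

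These figures assume one between-arm test per outcome, independent units, Wilcoxon as a two-sample rank test between arms, and correlations from 0 to 0.8 that the protocol does not supply. For the QEHD the protocol does not make clear whether Wilcoxon compares arms or compares before with after.

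A reader might also infer that the tooth-versus-participant question is part of this defect. It is a separate issue: none of the figures includes clustering of teeth, and this point does not depend on it.

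**What to change.** **Sections 5 and 6.9, outcomes.** Name one primary outcome consistent with 6.3: VAS for one named stimulus, with one month as the final assessment, and state the between-arm test that decides it at 5%. Air is a reasonable example, because 6.8.1 fixes its pressure, duration and distance. Then test the other stimulus and the QEHD in a stated fixed order, each only if the one before it rejects. If the three are to stay co-equal, test each at 0.0167 instead. Either way, specify the QEHD test as a between-arm comparison, and word the hypothesis in section 5 to match.

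**Section 6.9, fallback.** Add an overall between-arm rank test, followed by multiplicity-adjusted pairwise comparisons. Tukey can stay as it is on the parametric route.

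**Cost.** This changes protocol wording only, with no new visits or measurements. With the fixed order, a positive result on a secondary outcome alone no longer rejects the main hypothesis. Splitting alpha lowers power for each outcome by an amount that cannot be computed, because 6.3 gives no VAS standard deviation or effect size f. The mixed ANOVA and the unit of analysis are not changed by this fix.
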